##### Initial session

During the initial session, participants will be taught how to perform upper limb exercises from the Home GRASP protocol by a trained physical or occupational therapist over the Zoom software platform (Zoom Video Communications). The participants will be instructed to complete the prescribed exercises twice per day (or a minimum of 2 h/day). A binder containing verbal and pictorial instructions for each exercise and a kit with the equipment required to complete the exercises will be mailed to the participant. In addition, the TENZR and a tablet will be included in the mailed package. The TENZR does not have any visual display, and the hand counts and target (set by the therapist) are shown on an app on the tablet (see Fig. 2 of the TENZR and app). The participants will be provided with education around the importance of incorporating the affected upper limb into daily activities. The therapist will also discuss strategies for incorporating the affected upper limb into daily activities and will be provided with a checklist of example activities (e.g. open door) in which their upper limb can be used. Participants will be asked to wear the TENZR device during waking hours and to recharge the device overnight. Finally, the participants will be shown how to navigate the TENZR app on a tablet.

**Fig. 2 Fig2:**
[figure not shown]
TENZR wrist-worn sensor and app. **a** TENZR wrist-worn sensor. **b** App showing a target of 1000 hand counts with 408 completed. **c** App showing a target of 1000 hand counts with 1029 completed

##### Follow-up sessions

Participants will be asked to take part in five follow-up sessions virtually after the initial session to monitor their adherence to the exercise program, ability to meet daily movement targets and to progress their exercises and movement targets. At the second session, the therapist will set daily movement targets in collaboration with the participant based on the average daily hand counts captured by the TENZR based on the baseline counts, as well as counts since the initial session. See the “Evaluations” section for the definition of a hand count. The following suggested guidelines will be provided to therapists for setting daily movement targets. If the daily baseline hand counts are less than 1000, then a target for 1000 daily hand counts will be set. If the daily baseline hand counts are greater than 1000, an additional 20% will be added. A minimum of 1000 hand counts will be set. Therapists may modify the exercises and daily activities to accommodate fatigue and/or pain.

The tablet will show the daily total GRASP counts and participants will then record these values in a 1-page summary sheet and review with their therapists at each session. Therapists will prompt participants to identify barriers to meeting movement targets and will assist participants to problem solve solutions to overcoming those barriers. The logging of the GRASP counts and discussion of strategies to increase GRASP counts will serve as a mechanism of accountability and adherence to the protocol. At the final session, the therapist will discuss recommendations for further arm activity.

The components of the V-ABC were designed to address considerations outlined in the Capability, Opportunity, Motivation, Behaviour Model applied to affected upper limb use after stroke [14]. This is a model of behaviour described in the Behaviour Change Wheel Framework [15]. The framework helps guide the development of behaviour change interventions. Table 1 outlines the Capability, Opportunity, Motivation, Behaviour Model applied to the affected upper limb use during daily activities. The information for this table was obtained from the literature and through our experience studying upper limb use post stroke.

**Table 1 Tab1:** Capability, Opportunity, Motivation, Behaviour Model Components of the intervention

What needs to happen so that the affected arm is used?	Methods to address components
**Capability: Physical**	
Person needs to have enough arm function to be able to use the limb in a helpful way	• GRASP Exercise Program
**Capability: Psychological**	
• Understands the evidence related to experience-driven neuroplasticity • Understands the importance of “use it or lose it”; • Understands the importance of challenge and practice • Has emotional resilience to practice despite frustration • Has ability to problem solve when encountering problems using the limb • Has ability to monitor how and how much they are using limb • Knows how to advance task practice • Patient has sufficient memory/attention/executive function to develop and adhere to practice schedule	• Education of link between challenging practice and neuroplasticity • Feedback from TENZR • Action planning • Goal setting • Barrier identification and problem solving
**Opportunity: Physical**	
• Patient has time to use upper limb as tasks will take longer • Patient has appropriate items in the house or community to enable task practice • Patient has external reminders to use the limb	• Problem solving • Feedback from TENZR
**Opportunity: Social**	
• Has a person who will support patient while he/she is less efficient in accomplishing tasks during and after intervention • Patients not entirely driven to accomplish tasks independently no matter what • Social pressure to perform activities as before the stroke	• Social support from therapist • Social support from family
**Motivation: Reflective**	
• Believe that incorporation of their arm into daily activities will improve their function • Believe that practicing using their arm is important • Believe that temporary frustration will lead to positive gains • Be confident that their affected arm can accomplish required task • People have goals for using their limb (i.e. tasks they wish to change or start doing) • Have intentions to increase practice or use in daily activities	• Education of link between challenging practice and neuroplasticity
**Motivation: Automatic**	
• Have established routines and habits for using limb • Experience emotional benefits from using their limb	• Problem solving and planning

#### Evaluations

Participants randomized to the immediate treatment group will undergo 3 assessments through Zoom software: (1) upon admission to the study (baseline assessment), (2) immediately following completion of the treatment (post-intervention) and (3) 2 months following completion of the treatment (retention). Participants randomized to the delayed treatment group will undergo 4 assessments: (1) upon admission to the study (baseline assessment), (2) 3 weeks post baseline, (3) immediately following treatment (post-treatment) and (4) 2 months following completion of the treatment (retention). Evaluators will be occupational or physical therapists who will participate in about 4 h of training (reviewing materials and an online training session). They will be blinded to group allocation of the participant, i.e. immediate vs delayed. Participants will be instructed not to reveal their group to the evaluator. See Table 2 for the schedule of enrolment and timing of the evaluations.

**Table 2 Tab2:** Schedule of enrolment and evaluations

Study procedures	Screening	Baseline evaluation	Post-intervention evaluation	Two-month evaluation
Timepoint	− *T*_1_	*T*_0_	*T*_1_	*T*_2_
Informed consent	+			
Inclusion/exclusion criteria	+			
Demographics		+		
Randomization		+		
Primary outcome measure				
3-day hand counts		+	+	+
Secondary outcome measures				
Impairment				
Upper limb pain		+	+	+
Functional				
Arm Capacity and Movement Test (upper limb functional capacity)		+	+	+
REACH Scale (self-reported arm use)		+	+	+
Stroke impact scale—arm function		+	+	+
Stroke impact scale—arm strength		+	+	+
Adverse events		+*	+*	+*

*indicates that the measure will be taken or monitored throughout the intervention period

Participants will be reminded about follow-up appointments at each appointment, in addition to a reminder immediately before the appointment by phone, text or email, depending on the participant’s preference. In addition, a secondary contact of the participant will be collected in case the participant cannot be contacted at their primary contact number.

Personal information (name, contact information) as well as demographic data (age, sex) will be collected from the participant, and medical history will be extracted from their medical chart upon consent from the participant to access their health records. Participants will be assigned a subject number that is not derived from personal information. Personal information of participants will be kept separately from the trial data and not shared between sites. No identifying information will be published or released. The data will be coded by project name and a unique alphanumeric subject number. Personal identifiers (name initials) will not be used, nor will subject number be derived from personal identifiers. Only de-identified data necessary for data analysis (demographic and assessment data) will be sent to the coordinating site, by courier or by encrypted, password-protected files. All paper data will be stored according to the university research ethics board standards (i.e. in locked cabinets within locked research offices), and electronic data will be encrypted and stored on a password-protected university server. Data entry will be carried out by a research assistant, with electronic range checks for data values, and verified by a member of the steering committee. On the consent form, participants will be informed that they can withdraw their data should they choose to withdraw from the trial.

#### Primary outcome

Study staff will document any circumstances leading to the discontinuation or modification of treatment. Regardless of whether a participant modifies or discontinues the intervention, study participants will be retained in the trial whenever possible to enable follow-up data collection of all outcome measures and prevent missing data.

Participants will be asked to wear the TENZR device on the affected upper limb for 3 days at each assessment time. Feedback from the TENZR device shown on the tablet will be inactivated during the assessment. The average daily hand counts from this 3-day assessment immediately following the 3-week intervention will be the primary outcome. This wrist-worn sensor is able to consistently capture functional reach to grasp repetitions in individuals with mild to moderate upper limb stroke impairment and has good validity, as well as good agreement over two test sessions [16]. The device uses a multi-sensor sensing approach to detect reach-to-grasp activity. Force myography is used to detect the state of the hand by monitoring the surface forces on the wrist musculo-tendonous complex proximal to the hand. The system outputs one hand count when it detects a functional reach-to-grasp movement. This is defined as any finger/grip and wrist activity which is accompanied by inertial movements of the arm before or after the hand/wrist motion [16]. For example, turning a door knob results in 1–2 hand counts; one count on reaching forward, opening the hand and grasping the door knob, and a second count can occur if there is a distinct hand opening on letting go of the door knob and withdraw of the arm. The combination of an arm reaching movement and a hand grasping/releasing movement approximates the initial interaction with an object (i.e. reach and grasp) and/or final interaction with an object (i.e. release and arm move away).

#### Secondary outcomes

##### Self-report affected arm use

The REACH Scale is a valid and reliable tool for capturing how people are using their affected arm and hand outside in the community setting [12].

##### Upper limb functional capacity

The Arm Capacity and Movement Test was developed by our research team to capture participants’ ability to use their affected upper limb virtually and has been shown to be valid and reliable [17].

##### Upper limb pain

A 0–10 visual analogue pain scale will be used to capture upper limb pain throughout the treatment and at each assessment time point. This measure has been shown to be valid and reliable across many different populations [18].

##### Stroke specific health quality of life (strength and arm function subscales)

Two subscales of the *Stroke Impact Scale* (SIS) will be used to capture the impact of stroke on participants’ strength and arm function. The SIS has excellent measurement properties for people with stroke [19].

#### Data monitoring

All sites will report minor and serious adverse events that occur from baseline through to the 2-month follow-up. An internal Data Safety Monitoring Board comprised of 5 physical medicine physicians will be notified of adverse events when they arise. An internal board is deemed to match the low risk of this trial. No interim analyses will be done and there will be no stopping rule for the trial because it is not anticipated that any serious adverse events would result from the protocol. Protocol modifications will be communicated to investigators and trial staff via email and discussed at the weekly meetings, and documentation will be updated as appropriate (e.g. updated protocol, amendments and approval by the ethics board, update of the clinical trial registry protocol). Participants will be advised of protocol changes and invited to sign an amended consent form to indicate their continued consent to participate in the study.

#### Sample size estimates

The sample size was calculated using G power. The study will require 32 patients per group to achieve 80% power at a level of significance of 0.05 to detect a large effect size (Cohen’s *f* = 0.4) using an ANCOVA model (controlling for baseline values) and a dropout rate of 20%.

#### Data analyses

Descriptive statistics will be used to summarize data. Analysis of covariance will be used for the main analysis to estimate the differences comparing the 3-day hand counts at the post-treatment (immediately following the 3-week intervention) controlling for the baseline. Multiple imputation will account for missing data. The significance level will be set at 0.05, and all statistical tests will be two-tailed. Participant data will be analysed on an intention-to-treat basis. Confidence intervals (95% CIs) will be reported, where applicable. Secondary outcomes at post-treatment will follow the same analysis. In an additional analysis, we will use a mixed effects model to examine whether the intervention effects are retained at 2 months after the intervention ends.

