#### Randomization

Participants will be randomized after their baseline assessment at a one-to-one ratio to either the Immediate Virtual Arm Boot Camp (V-ABC) group or Delayed V-ABC group using an online, third-party, randomization service (www.randomize.net). Randomization will be in variable block sizes (to ensure allocation concealment) and stratified by site (to control for regional differences). Participants will also be stratified by the REACH score (< 3 and ≥ 3) [12]. A score of 3 separates those with mild versus moderately affected upper limbs.

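### Randomisation is stratified by site and REACH but the stated ANCOVA names only the baseline value, so the test is conservative to the extent that these factors predict the outcome beyond baseline

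*Protocol article*

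**What the plan says.** The Randomization section of the protocol article restricts allocation on two factors. Allocation is "stratified by site (to control for regional differences", and "Participants will also be stratified by the REACH score", with a cut at 3 that is said to divide mild from moderate impairment. Seven sites and two REACH levels give 14 strata.

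The model is described twice. The Data analyses section states: "Analysis of covariance will be used for the main analysis to estimate the differences comparing the 3-day hand counts", measured after treatment, with control for the baseline. The Sample size estimates section says the size was found "using an ANCOVA model (controlling for baseline values". Secondary outcomes after treatment are to be analysed in the same way, and missing data are to be multiply imputed. Neither description of the model mentions site or REACH, and neither says in so many words that the baseline is the only covariate.

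**The concern.** Stratified allocation makes the arms alike on site and REACH. If these factors carry prognostic information beyond the baseline value, the treatment estimate varies less from trial to trial than under simple randomisation. A model that leaves them out does not recognise this: their variance stays in the error term, the reported standard error exceeds the true one, and p-values and confidence intervals are too cautious. The investigators evidently thought both factors worth controlling, since they built them into the design.

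What is at stake is efficiency in a small trial: confidence intervals wider than they need be, and power left unused. The same applies to the secondary outcomes. For most of these the baseline covariate is a different measure from REACH, so it need not absorb the REACH stratum.

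**Working it through.** **Inputs from the protocol article.** Two-sided α 0.05, power 80%, Cohen's f = 0.4 (d = 0.8 for two equal groups), 32 per group, 20% dropout, 1:1 allocation, 7 sites, 2 REACH levels.

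**Input not given.** R², the share of the residual variance (after baseline adjustment) explained by site and REACH together. It is assumed here over 0 to 0.30.

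**1. The plan's own figure.** For ANCOVA with k covariates, λ = f²N with 1 and N − 2 − k degrees of freedom. With k = 1 and N = 52, λ = 0.16 × 52 = 8.32 on 1 and 49 df, and power is 0.807. At N = 51 it is 0.799. So 26 evaluable per group are needed. Allowing for dropout, 26 × 1.2 = 31.2, rounded up to 32 (the stated figure); 26 / 0.8 = 32.5 would round to 33. The stated size therefore reproduces, to within one per group, for the baseline-adjusted model.

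**2. Size of the effect under perfect balance.** If the strata were perfectly balanced, true SE / model SE for the baseline-only analysis would be √(1 − R²): 0.949, 0.894 and 0.837 at R² = 0.10, 0.20 and 0.30. Balance will be imperfect: 64 / 14 = 4.6 randomised per stratum and 52 / 14 = 3.7 analysed, so many blocks stay incomplete. Simulation is needed.

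**3. Simulation.** Settings: 64 randomised in blocks of 2 or 4 within 14 strata; 52 analysed after random dropout; 4,000 runs per setting. Assumptions: sites equal in size on average, REACH split 50:50, R² shared equally between site and REACH, baseline–outcome correlation 0.6. The total residual variance is held at the planned value, so f = 0.4 keeps its meaning. Standard errors are under the null, in residual SD units.

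| R² | Baseline only: model SE / true SE | SE overstated by | Baseline only: type I error | Power: baseline only | Power: + REACH | Power: + REACH + 6 site terms |
|---|---|---|---|---|---|---|
| 0 | 0.281 / 0.281 | 0% | 5.1% | 80.0% | 79.7% | 77.5% |
| 0.05 | 0.282 / 0.280 | 1% | 4.6% | 79.6% | 80.5% | 78.9% |
| 0.10 | 0.282 / 0.270 | 4% | 3.9% | 80.9% | 83.0% | 82.2% |
| 0.20 | 0.282 / 0.261 | 8% | 3.6% | 80.0% | 83.5% | 84.9% |
| 0.30 | 0.281 / 0.247 | 14% | 2.6% | 82.6% | 87.5% | 90.6% |

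Monte Carlo error is about √(0.05 × 0.95 / 4000) = 0.3 points for type I error and √(0.8 × 0.2 / 4000) = 0.6 points for power. A repeat simulation gave 4.6% at R² = 0 and 2.8% at R² = 0.30 for the baseline-only type I error.

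If all of R² lies in REACH, then at R² = 0.20 baseline-only type I error is 3.1%, and power is 81.3% (baseline only), 87.8% (+ REACH) and 85.8% (+ REACH and site).

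**4. Cost of six fixed site terms.** By formula, eight covariates leave 52 − 2 − 8 = 42 df, and power goes from 0.807 to 0.805. That counts only the lost degrees of freedom. In simulation at R² = 0 the true SE rises from 0.2813 to 0.2886, a factor of 1.026, because with such small strata the site terms are not orthogonal to arm. The real cost is 80.0 − 77.5 = 2.5 points. REACH alone costs 80.0 − 79.7 = 0.3 points here, and 0.5 points in a second simulation with 51 analysed (79.4% to 78.9%).

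**The case against.** The article condenses a fuller protocol, and no SAP is shown. The complete covariate list may be there, and naming the main covariate in a summary does not contradict stratified allocation. This limits the point but does not remove it: the article describes the model twice, consistently, and the design it reports supports a better model with data already collected.

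REACH is self-reported use of the affected arm, and the hand count measures use of that arm, so the baseline count may absorb much of REACH. This stands. At R² of 0.05 or less the standard error is overstated by no more than about 1%, and full fixed-effect adjustment would lose power.

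Three stronger readings are tempting, and the documents support none of them.

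- A reader might infer that power falls below the stated 80%. But f = 0.4 was specified for the baseline-adjusted ANCOVA, whose error term already contains any site and REACH variance. Simulations that show power in the low 70s add that variance on top of the planned residual. Raising the residual variance by about 15% shrinks f to 0.4 / √1.15 = 0.373, and at N = 51 the formula then gives 74.2%. With the planned residual variance kept, baseline-only power stays at about 79% to 83%.
- A reader might infer that the standard error is certainly too large. That requires R² to be appreciably above zero, which the documents do not establish.
- A reader might take chance imbalance within strata for bias. Under randomisation the baseline-only estimate is unbiased, and such imbalance is part of its sampling variance.

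**Conclusion.** The point holds in conditional form. The stated ANCOVA omits the factors on which randomisation was restricted. If REACH and site explain an assumed 10% to 30% of the residual variance, the standard error is overstated by about 4% to 14% and the true type I error is about 4% falling to about 2.7%. Adding REACH alone would then gain about 2 to 5 points of power (80.9% to 83.0%; 82.6% to 87.5%). The direction is certain if the factors are prognostic; the size is not, because R² is assumed. The results also rest on the simulation settings above, including analysis of 52 completers rather than imputed data. There is no inflation of false positives, no bias, and no threat to the planned power of the baseline-adjusted analysis. The change is worth making because it is cheap, and because covariates chosen after the data are seen would be open to challenge.

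**What to change.** In the Data analyses section, define the primary and secondary ANCOVA as arm, baseline value of the outcome and REACH stratum (< 3, ≥ 3), with site as a random effect or pooled into a few groups by a rule fixed before unblinding, rather than as six fixed terms. Put the same terms in the imputation model. When the REACH scale is itself the outcome, its baseline score already carries most of the stratum, so little is gained there and little is lost. If the full protocol or SAP already names these covariates, it is enough for the published text to say so.

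The change takes a sentence or two and no new data. If the factors prove uninformative, REACH alone costs about half a point of power; six fixed site terms with REACH would cost about 2 to 3 points, which is the reason for a random or pooled site effect. The random-effect version was not simulated. Its cost should be smaller than that of the fixed terms, because it shrinks towards no adjustment when sites differ little.

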### Qualitative component: qualitative description

A qualitative descriptive study will be conducted alongside with the RCT to explore patients’ views and experiences of the virtual ABC program, including the TENZR activity monitor, GRASP exercises, therapy sessions and trying to use their affected arms more during daily activities. The qualitative description methodology is widely used for research questions focusing on understanding patients’ experiences, particularly for examining healthcare phenomena [20]. It is a rigorous methodology that provides a comprehensive and straight description of an experience without the need to apply a certain theory or framework [21]. The consolidated criteria for reporting qualitative research guidelines was used to inform the qualitative design and will be used to report the qualitative data to ensure methodological quality and transparent reporting [22].

